### Autonomic ECG Markers

In addition to routine 12-lead ECG at admission and stroke unit monitoring, included patients receive an additional 20-min high-resolution resting ECG during the first day after enrollment using the portable medilog AR4+ device (Schiller AG). The aim is to measure specific autonomic markers periodic repolarization dynamics (PRD) and deceleration capacity (DC), reflecting sympathetic and vagal components of cardiac autonomic function in addition to standard measures of heart rate variability (HRV) in time and frequency domain [29-31]. The 7 electrodes of the high-resolution ECG are applied according to the Frank lead configuration in the 3 orthogonal axes X, Y, and Z. The examination is performed under standardized conditions (supine position, patient is not allowed to talk or change the position during the recording). For analysis, the pseudonymized ECG data are transmitted to the core lab of the academic working group *biosignal analysis* ([name] [name]) at the cardiology department of the Medical University of Innsbruck, Austria. Members of the working group analyzing the data are blinded to all clinical information.

### Biobanking

The study protocol includes an additional blood examination for biobanking to allow future study of further potential mechanisms. Blood drawing takes place during the first day after enrollment and includes 2 EDTA (for both whole blood and plasma samples), 1 heparin, 1 coagulation sodium citrate, and 1 serum tube. Blood withdrawal, centrifugation, and processing will be conducted by a trained study nurse. Blood samples are transferred to the Central Biomaterial Bank Charité for management and storage. After processing, the stored samples consist of 5.7 mL of EDTA whole blood; 1.5 mL of citrate plasma; and 2 mL of EDTA plasma, heparinized plasma, and serum samples each. These samples will allow measurement of various potential biomarkers of interest. Dependent on further funding, we consider to determine biomarkers of cardiac injury and stress, proinflammatory markers, and markers of endothelial dysfunction (such as N-terminal B-type natriuretic peptide [NT-proBNP], midregional proatrial natriuretic peptide [MRproANP], Copeptin, interleukin-6, interleukin-1β, Soluble suppression of tumorigenicity 2 [sST2], and monocyte chemoattractant protein-1 [MCP-1]). Furthermore, we consider exploring whether patients with signs of stroke-associated myocardial injury present distinct miRNA-pattern. Finally, the design allows future cooperation with other research groups.

### Follow-Up Telephone Interview

A follow-up regarding major cardiovascular events takes place 3 and 12 months after enrollment via telephone interview and is conducted by a trained participant of the research group. A major cardiovascular event is defined as the occurrence of transient ischemic attack and ischemic stroke, intracranial hemorrhage, MI, coronary artery bypass surgery or percutaneous coronary intervention, new atrial fibrillation, hospitalization for heart failure, and death. The functional outcome is assessed using the modified Rankin Scale. In case of death, the date of death is recorded using information from registration offices. In the case of cardiovascular events, medical records will be requested from the treating physician/institution. Furthermore, Charité records will be screened for readmission or further treatment. In case of unclear loss to follow-up, mortality status will be retrieved from the residents’ registration office.

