## Introduction

### Background

Elevated cardiac troponin (cTn), which is a sign of myocardial injury, frequently occurs in the early phase after an acute ischemic stroke (AIS) and is associated with poor functional outcome, especially increased mortality [1,2]. Using high-sensitivity assays, cTn is detectable in more than 90% of stroke patients; 30%-60% have at least one cTn above the assay-specific 99th percentile upper reference limit (URL) [2,3]. Approximately 5%-20% show a rise/fall pattern indicating acute myocardial injury according to the fourth universal definition of myocardial infarction (MI) [4]. In the latter group, acute coronary syndrome has to be suspected [4-6]. Following the American guidelines (American Heart Association/American Stroke Association), it is specifically recommended to measure cTn in stroke patients [7,8]. However, recommendations on how to deal with elevated cTn in the context of AIS remain vague [8]. Furthermore, expert consensus documents on practical considerations on the clinical use of cTn list ischemic stroke as one of the illnesses that leads to clinical uncertainty in the context of interpretation of elevated cTn [9].

The phenomenon of acute brain injuries (including an ischemic stroke and intracranial hemorrhage) leading to cardiac complications, including elevated cardiac enzymes, is known for a long time. In reference to AIS, it has recently been described as stroke-heart syndrome (SHS) [10-13]. However, the exact pathophysiologic background of myocardial injury (ie, cTn elevation) after stroke is not entirely understood [13,14]. Several hypotheses have been discussed. Besides concomitant acute MI caused by atherothrombotic coronary artery disease (type 1 MI), situations of oxygen supply/demand mismatch have to be considered as underlying reasons. For example, tachyarrhythmia, hypotension/shock, anemia, or respiratory failure, which are frequently seen in stroke patients, can lead to a demand ischemia [4,15]. Furthermore, systemic conditions such as sepsis or chronic kidney disease may cause or facilitate myocardial injury [16].

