## Methods

### Study Design

The CORONA-IS study is an investigator-initiated, prospective, observational, single-center cohort study that aims to include 300 patients with AIS. In November 2018, the Ethics Committee of the Charité-Universitätsmedizin Berlin, Germany (EA4/123/18), approved the study. All study procedures are carried out in accordance with the principles of Good Clinical Practice and the Declaration of Helsinki. The study was pre-registered under clinicaltrials.gov, NCT03892226. All patients with AIS admitted to the hospital within 48 hours of symptom onset are listed in a hospital-based registry as part of an assessment of high-sensitivity cTn (hs-cTn) development in patients with AIS. All study patients have to fulfill the study inclusion criteria listed in Textbox 1, and all participants have to provide written informed consent (for exclusion criteria refer to Textbox 2).

Inclusion criteria.ability to provide informed consentage ≥18 yearsdiagnosis of acute ischemic stroke and hospital admission within 48 hours of symptom onsetvisible diffusion-weighted imaging lesion in cerebral magnetic resonance imagingrepeated measurement of high-sensitivity cardiac troponin within 24 hours of admission

Exclusion criteria.pregnancy or breastfeedingimpaired renal function (estimated glomerular filtration rate <30 ml/min/1.73 m^2^)contraindications to undergo magnetic resonance imaging (eg, cardiac pacemaker, implantable cardioverter-defibrillator, and cerebral clips)persistent or permanent atrial fibrillation (patients with paroxysmal atrial fibrillation will be included if they are in sinus rhythm at admission or during cardiac monitoring of the stroke unit)ST-elevation in electrocardiogram fulfilling criteria of myocardial ischemiahistory of cardiac intervention (eg, coronary artery bypass surgery or percutaneous coronary intervention) within the last 4 weeks

Depending on serial measurements of hs-cTn during the acute hospital stay (assay characteristics: hs troponin T, Roche Elecsys, Gen 5; 99th percentile upper reference limit=14 ng/l; 10% coefficients of variation (CV) precision=13 ng/l; limit of detection=5 ng/l) and according to the fourth universal definition of MI, 3 groups are defined (Table 1) [4]. We aim to include 100 patients in each group. The cTn values are based on at least two blood exams: the first one at hospital admission and a control measurement within 24 hours after admission.

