**Table 1 table1:** Definition of the 3 groups based on patients’ high-sensitivity cardiac troponin values.

Group	Description	hs-cTn^a^ values (URL^b^=14 ng/l)
Group 1	Normal hs-cTn levels	Both hs-cTn levels ≤URL
Group 2	Chronic myocardial injury (elevated but stable cTn levels)	At least one hs-cTn level >URL but *no* rise/fall (>20%) in serial measurements
Group 3	Acute myocardial injury (dynamic elevation)	At least one hs-cTn level >URL *and* rise/fall (>20%) in serial measurements^c^

^a^hs-cTn: high-sensitivity cardiac troponin.

^b^URL: upper reference limit (=14 ng/l).

^c^Or initial cTn value ≤URL and second value >URL+increase >50% URL (ie, 7 ng/l).

In addition to routine clinical procedures (refer to the *Baseline Visit* section), study patients receive a baseline assessment, an additional blood draw for biobanking, 3 Tesla (3T) cardiovascular magnetic resonance imaging (CMR), transthoracic echocardiography (TTE), and a 20-min high-resolution electrocardiogram (ECG) for a comprehensive assessment of cardiac autonomic function as well as a questionnaire testing cognitive function and the perception of stress. Furthermore, 3 and 12 months after discharge, patients will be followed up via structured telephone interviews for cardiovascular events and clinical outcomes (Figure 1).

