**Figure 2 figure2:**
[figure not shown]
3T cardiovascular magnetic resonance imaging protocol. Workflow of the cardiovascular magnetic resonance imaging sequences conducted. 2Ch: 2-chamber view; 3Ch: 3-chamber view; 4Ch: 4-chamber view; 3T: 3 Tesla; LGE: late gadolinium enhancement; mv: midventricular; SAX: short axis view; SSPF: steady-state free-precession.

Finally, for further myocardial tissue characterization, motion-corrected *T1 mapping* based on the Modified look-locker inversion recovery technique (MOLLI) using a 3-3-5 pattern is performed before and 15 min after contrast media application in 4Ch view and 3 short axes with basal, medial, and apical slices (imaging parameters: TR: 281.64 ms (4Ch) and 332.67 ms (SAX), TE: 1.12 ms, slice thickness: 6.0 mm, and Generalized Autocalibrating Partial Parallel Acquisition (GRAPPA) acceleration factor: 2).

Pseudonymized CMR data are transferred to the core Lab *AG Kardiale MRT* ([name] [name]) at the Department of Cardiology, Charité Campus Buch (Berlin), for further analysis. Experienced readers (Society for Cardiovascular Magnetic Resonance level III) analyzing the MR data are blinded to the clinical data. The clinical results are provided to the study patient, and in case of pathological findings that require further diagnostics or treatment, the clinical results are provided to the patients’ treating physician.

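### Any coronary revascularization counts as a follow-up event, although the troponin pattern that defines group 3 is itself a reason to suspect acute coronary syndrome

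*Protocol article*

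**What the plan says.** The Follow-Up Telephone Interview section lists the components of a major cardiovascular event. MI and the cerebrovascular events (stroke, TIA, bleeding within the skull) are named first, and the rest of the list reads "coronary artery bypass surgery or percutaneous coronary intervention, new atrial fibrillation, hospitalization for heart failure, and death". All rank equally, and nothing is said about the indication for a procedure. Textbox 3 makes the frequency of these events at 3 and 12 months a secondary outcome. The statistical section plans chi-square comparisons of primary and secondary outcome measures across the three troponin groups.

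Table 1 defines group 3 by at least one hs-cTn value above 14 ng/l together with a change of more than 20%, or by a rise from a normal first value that meets its footnote. On patients with a rise/fall pattern the Background states: "In the latter group, acute coronary syndrome has to be suspected".

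The Cardiovascular MRI Protocol section adds a route to the treating physician: "in case of pathological findings that require further diagnostics or treatment, the clinical results are provided to" that physician. This applies to every group.

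The start of follow-up is given in two ways. The follow-up section says "A follow-up regarding major cardiovascular events takes place 3 and 12 months after enrollment via telephone interview"; Study Design says "3 and 12 months after discharge, patients will be followed up via structured telephone interviews".

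**The concern.** An outcome used to compare prognosis between exposure groups should not include actions that the exposure itself can prompt. Revascularization is decided by clinicians. The group 3 troponin pattern is, in the article's own words, a reason to suspect the condition for which revascularization is done. A procedure that completes the work-up of the index finding would then be recorded as a new event.

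If this happens more often in group 3, the event comparison mixes two things: a worse course after stroke-associated myocardial injury, and more coronary investigation and treatment because of the troponin result. The direction is predictable, towards more events in group 3. A reader could conclude that acute myocardial injury predicts cardiovascular events even if stroke, MI, heart failure and death were equally frequent in the groups. Blinded reading of CMR, TTE and ECG does not help, because the treating physician decides on the procedure.

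**Working it through.** **1. Can such a procedure enter the count?** The relevant rules, side by side:

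- Event definition (Follow-Up Telephone Interview): any bypass surgery or percutaneous intervention counts.
- Exclusions (Textbox 2 and Limitations): ST elevation, new left bundle branch block, and cardiac interventions in the 4 weeks before inclusion. A patient whose only sign of a coronary event is the troponin change stays in the cohort, and procedures after inclusion are not addressed.
- Capture: records are requested from the treating institution, and the study hospital's own records are screened for readmission or further treatment. Procedures are likely to be found.
- Window: if it opens at enrollment, a procedure during the index stay counts. If it opens at discharge, an index-stay procedure may fall outside, but one done after discharge on the strength of the index troponin or the CMR report still counts.

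So under either start date, the stated rule lets some work-up of the exposure count as outcome.

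**2. How large could it be?** The article gives no event or revascularization rate; its only planning rates are for myocardial edema. There is no figure to reproduce, and all rates below are assumptions.

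Let h be the risk of every other component, equal in both groups, and r the probability of a work-up-driven revascularization, independent of h. Then

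composite = 1 − (1 − h)(1 − r), and RR = composite in group 3 / composite in group 1.

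Example: h = 10%, r = 2% in group 1 and 5% in group 3. Group 1: 1 − 0.90 × 0.98 = 11.8%. Group 3: 1 − 0.90 × 0.95 = 14.5%. RR = 0.145 / 0.118 = 1.23.

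| h | r, group 1 | r, group 3 | Group 1 | Group 3 | RR |
|---|---|---|---|---|---|
| 10% | 1% | 5% | 10.9% | 14.5% | 1.33 |
| 10% | 2% | 5% | 11.8% | 14.5% | 1.23 |
| 10% | 1% | 10% | 10.9% | 19.0% | 1.74 |
| 10% | 2% | 10% | 11.8% | 19.0% | 1.61 |
| 15% | 1% | 5% | 15.85% | 19.25% | 1.21 |
| 15% | 2% | 5% | 16.7% | 19.25% | 1.15 |
| 15% | 1% | 10% | 15.85% | 23.5% | 1.48 |
| 15% | 2% | 10% | 16.7% | 23.5% | 1.41 |

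The RR runs from 1.15 to 1.74, where the true value is 1.0.

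**3. Would it show in a test?** Take 100 patients per group (the planned size), no work-up-driven procedures in group 1, and a two-sided 5% test with the normal approximation. The chance of a significant excess in group 3, which should be 2.5% if nothing differs, is:

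| h | r = 2% in group 3 | r = 5% | r = 10% |
|---|---|---|---|
| 10% | 6% | 16% | 44% |
| 15% | 5% | 12% | 33% |
| 20% | 5% | 10% | 26% |

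At 2% the distortion is slight (11.8% against 10% when h = 10%). At 10% it is material.

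**The case against.** The strongest reply is that the documents do not show that work-up differs between groups. The Background calls recommendations on elevated troponin in stroke vague. It also reports an angiography study in which half of the stroke patients with markedly elevated troponin had no coronary artery disease, and in which culprit lesions were less frequent than in matched coronary patients. Work-up-driven procedures may be few. This stands, and it is why no size can be claimed. It does not remove the point: suspicion of acute coronary syndrome is stated for exactly the pattern that defines group 3.

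It can also be said that the outcome is secondary in a mechanistic study, that the parenthesis in the statistical section names CMR, TTE and ECG alterations and so only implies an event comparison, and that component reporting and adjudication may be set out in a fuller plan. All of this is fair, and no weight is placed on missing adjudication detail. The component list, however, is stated in the article and is unconditional.

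Three stronger readings are tempting, but the article does not support them:

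- *New atrial fibrillation is triggered in the same way.* No section links rhythm monitoring to the troponin pattern or to CMR, and stroke unit monitoring is described as routine. The article does admit some patients with known paroxysmal arrhythmia ("patients with paroxysmal atrial fibrillation will be included if they are in sinus rhythm at admission or during cardiac monitoring of the stroke unit"), but that concerns what counts as new, which is a different matter.
- *The CMR report must favor events in group 3.* It goes out for all groups. Study Outcomes ties late enhancement to chronic injury and expects edema without it in stroke-associated injury. For recent MI the Discussion predicts no direction. Of the findings most likely to lead to a coronary procedure, none is predicted to be more frequent in group 3. Left ventricular dysfunction is, so a difference by this route is possible but not given.
- *The excess is built in because group 3 is sent for coronary work-up.* The text says that the diagnosis has to be suspected, not that any work-up follows.

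**Conclusion.** The point holds in a limited form. The event definition allows a revascularization prompted by the index troponin, or by the study CMR report, to count as a follow-up event. Because the troponin pattern defines group 3, this can inflate that group's event frequency. That the rule permits this is clear from the text; how far it matters is not. With the assumed rates above the RR lies between 1.15 and 1.74 under equal true risk. With rarer procedures the effect is negligible. The illustration rests on equal risk of the other components, independence of the two risks, and more work-up-driven procedures in group 3 than in group 1; the documents supply none of these figures. The primary CMR and TTE outcomes and the other secondary outcomes are untouched. The change is worth making because the direction of the possible bias is known and the remedy is cheap.

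**What to change.** In the Follow-Up Telephone Interview section and the analysis of this outcome:

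1. Record the date of and the reason for each revascularization, taken from the medical records that the section already requests.
2. Give the group comparison of events also without revascularizations prompted by the index troponin or the study CMR, at least as a prespecified sensitivity composite. Where possible, the person who classifies the reason should not know the troponin group.
3. Report revascularization and every other component separately by group.
4. Reconcile the start of follow-up (enrollment in this section, discharge in Study Design) and state whether procedures during the index stay count.

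The cost is two abstraction fields and a few lines of text. Patient care does not change. The narrower composite will have fewer events and somewhat wider confidence intervals. With 107 of 300 patients included at submission, most records were still to be collected.

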### Study Outcomes

Our main hypothesis is that the development of stroke-associated myocardial injury in patients with AIS is based on a stroke-related interference in the CAN resulting in myocardial tissue alterations and dysfunction (ie, stroke-induced "myocardial stunning") [13]. Using a systemic and multimodal diagnostic approach, we aim to provide a detailed characterization of myocardial tissue, cardiac function, and autonomic cardiac regulation (Figure 3). Thus, outcome measures are primarily based on cardiac tissue characterization via CMR, functional assessment using TTE and CMR measurements, and values of specific autonomic ECG markers. Textbox 3 shows the detailed outcome measures. In summary, as we assume that patients with stroke-associated myocardial injury show a Takotsubo syndrome (TTS)/stress cardiomyopathy pattern of lesions in the myocardium, we will focus on the presence of wall motion abnormalities together with myocardial edema (T2 mapping) but without corresponding LGE in CMR [32,33]. Left ventricular dysfunction and wall motion abnormalities will be measured via cine imaging in CMR and TTE. As a correlate of chronic myocardial injury, we further assess myocardial fibrosis/scar via LGE, diffuse fibrosis via T1 mapping, and extracellular volume fraction (ECV%) [34]. To facilitate the differentiation between stroke-induced and coronary-mediated myocardial injury, we evaluate typical CMR signs suggesting a recent MI (ie, presence of co-occurring LGE and acute edema in CMR). Infarcted myocardium will be defined as a region with a mean signal intensity >5SDs relative to the remote uninjured myocardium on LGE images [35].

**Figure 3 figure3:**
[figure not shown]
Diagnostic assessment of the Cardiomyocyte injury following Acute Ischemic Stroke study. Illustration of the target points of the multimodal diagnostic workup to provide a thorough phenotyping of patients with stroke-associated myocardial injury. cMRI: cerebral magnetic resonance imaging; ECG: electrocardiogram; MRI: magnetic resonance imaging; TTE: transthoracic echocardiography.

Study endpoints.Primary outcome measuresFrequency of Takotsubo syndrome pattern on cardiovascular magnetic resonance imaging (CMR); consisting of wall motion abnormalities together with myocardial edema (T2 mapping) but without late gadolinium enhancementFrequency and extent of myocardial edemaFrequency of recent myocardial infarction on CMRFrequency and extent of ischemic and nonischemic myocardial fibrosis according to late gadolinium enhancement imaging and according to extracellular volume fraction on T1 mappingFrequency of left ventricular dysfunction in CMR (ie, ejection fraction and end diastolic left ventricular volume)Frequency of impaired left ventricular systolic and diastolic function in the transthoracic echocardiographySecondary outcome measuresFrequency of pathologic values of Periodic Repolarization Dynamics (PRDs) and Deceleration Capacity (DC; PRD≥5.75 deg²; DC≤2.5 ms)Frequency of values corresponding to *high perceived stress* in the Perceived Stress Scale (values ranging from 27 to 40)Frequency of cardiovascular events after 3 and 12 monthsFunctional outcome after 3 and 12 months assessed using the modified Rankin Scale.

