### Baseline Visit

The baseline assessment of the study patients includes demographics, medical history, medication, and information about the current stroke (time of symptom onset, time of hospital admission, and treatment including thrombolysis or thrombectomy). Stroke severity is classified using the National Institutes of Health Scale Score. The degree of disability is assessed using the modified Rankin Scale score. The presence of chest pain and dyspnea at admission and before the event is documented. Cognitive function and the individual perception of stress will be assessed via 2 questionnaires: Perceived Stress Scale and Montreal-Cognitive-Assessment [23,24]. In addition, the results of routine diagnostic procedures and stroke unit monitoring (eg, vital signs, 12-lead ECG, laboratory results, cerebral computed tomography imaging/MRI, and ultrasound of the brain-supplying arteries) are recorded.

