### Sample Size Calculation and Statistical Analysis

Regarding the primary hypothesis and based on the published literature, we expect a rate of acute myocardial edema on T2 mapping in CMR in approximately 15% of patients with acute myocardial injury [17,36]. In the comparison groups with no or chronic myocardial injury, we expect a significantly lower rate (approximately 2%) presenting with acute myocardial edema [37].

To show a significant difference between the groups (two-sided α=.05), a sample size of 48 patients per group is required to reach a power of 80% and 89 patients per group for a power of 90%. Taking into consideration that in previous studies, due to impaired compliance or technical problems, the complete protocol of CMR could be realized only in approximately 85% of the study patients, we aim to include approximately 100-105 patients in each group.

Group comparisons (when comparing between the 3 groups) of the primary and secondary outcome measures (frequencies of specific alterations in CMR, TTE, and ECG) will be conducted using the chi-square test for categorical variables and, in case of continuous variables, using one-way analysis of variance or Kruskal-Wallis test, as appropriate. When comparing 2 groups (group 3 vs group 1 or group 3 vs group 2), Student *t* test will be used to compare continuous data. Logistic regression analyses will be used to calculate odds ratios and 95% CI to examine the association between elevated hs-cTn levels and the presence of specific structural and functional cardiac alterations in CMR and TTE. Multiple regression analyses using backward selection will be used to identify factors associated with certain myocardial alterations or ECG findings.

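### Perceived stress is listed only as the share of patients scoring 27-40; analysing the total score, which is already collected, would be more efficient

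*Protocol article*

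**What the plan says.** Textbox 3 (study endpoints, under Study Outcomes) names a single perceived-stress outcome among the secondary measures: how often patients fall in the high band "in the Perceived Stress Scale (values ranging from 27 to 40"). That is a yes/no outcome per patient. For oedema and for fibrosis the same textbox lists both how often they occur and how extensive they are, so a quantitative measure was named there and not for stress.

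The underlying score will exist. The Baseline Visit section states: "Cognitive function and the individual perception of stress will be assessed via 2 questionnaires: Perceived Stress Scale and Montreal-Cognitive-Assessment".

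Sample Size Calculation and Statistical Analysis assigns the chi-square test to categorical outcomes. Continuous outcomes are compared across the three groups "using one-way analysis of variance or Kruskal-Wallis test, as appropriate", and between two groups by Student t test. The section does not mention the Perceived Stress Scale by name. Its only power calculation concerns myocardial oedema on T2 mapping. Under Study Design the target is stated as: "We aim to include 100 patients in each group".

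**The concern.** The cut reduces a graded score to one bit. A patient just below 27 counts the same as one with a very low score, and differences within the high band disappear as well. If few patients reach 27, the comparison rests on a handful of them, and a moderate shift in perceived stress between the troponin groups could be missed even though the collected scores would show it. A null result on the share scoring high would then say little about whether perceived stress differs between the groups. Since the listed outcome is the dichotomy, a later analysis of the full score would not be the outcome that was set in advance.

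**Working it through.** **The plan's own figure.** There is none for this outcome. The stated 48 and 89 patients per group (80% and 90% power) are for oedema at 15% versus 2%, so they neither support nor contradict anything about the stress score.

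**Inputs from the article.** 100 patients per group (Study Design); two-sided α of 0.05 (stated for oedema and borrowed here); cut at 27.

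**Assumed inputs, because the article gives none.** A normal score with equal SD in the groups; a difference between two groups of d standard deviations; a share p of the lower-scoring group at 27 or above, varied from 2% to 20%. A questionnaire score is discrete and bounded, so the normal model is an approximation.

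**Step 1: information kept by a cut.** For small shifts, the efficiency of the dichotomy relative to the full score is φ(c)² / [p(1−p)], where c is the normal quantile with upper tail p.
- p = 5%: c = 1.645, φ(c) = 0.1031, so 0.01064 / 0.0475 = 0.22.
- p = 10%: c = 1.282, φ(c) = 0.1755, so 0.0308 / 0.09 = 0.34.
- p = 50%, the best case: 0.1592 / 0.25 = 0.64.
- Efficiency equals 0.50 at p ≈ 20.9%.

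So every cut loses at least about 36%, and more than half is lost when fewer than about 21% score high.

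**Step 2: power on the full score.** Power = Φ(d√(n/2) − 1.960). With d = 0.4 and n = 100, this is Φ(2.828 − 1.960) = Φ(0.868) = 80.7%. The n per group for 80% power is 2(1.960 + 0.842)² / 0.16 = 98.1, that is 99.

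**Step 3: power on the dichotomy.** The higher-scoring group has a share p₂ = 1 − Φ(c − d) above the cut, and the two shares are compared by the usual pooled two-proportion test. Example with p = 5%, d = 0.4:
- p₂ = 1 − Φ(1.245) = 10.7%, so the difference is 0.0566.
- The standard error is 0.0380 under no difference and 0.0378 under the alternative.
- Power = Φ[(0.0566 − 1.960 × 0.0380) / 0.0378] = Φ(−0.47) = 31.8%.

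**Results, two groups of 100, two-sided 0.05**

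| Outcome | Share high in higher-scoring group, d = 0.4 | Efficiency | Power, d = 0.4 | Power, d = 0.5 | n per group for 80%, d = 0.4 | d giving 80% at n = 100 |
|---|---|---|---|---|---|---|
| Full score | – | 1 | 80.7% | 94.2% | 99 | 0.40 |
| Cut, p = 2% | 4.9% | 0.12 | 20.1% | 30.3% | 618 | 0.88 |
| Cut, p = 5% | 10.7% | 0.22 | 31.8% | 47.6% | 353 | 0.71 |
| Cut, p = 10% | 18.9% | 0.34 | 43.2% | 62.3% | 244 | 0.61 |
| Cut, p = 20% | 32.9% | 0.49 | 54.6% | 74.6% | 182 | 0.53 |

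**Step 4: sensitivity to the assumed difference.**
- d = 0.2: full score 29.3%, dichotomy 7.6% to 17.2%.
- d = 0.3: full score 56.4%, dichotomy 12.7% to 33.7%.
- d = 0.8: full score about 100%, dichotomy 70.2% to 99.1%.

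The full score is ahead throughout, but the gap is widest for moderate differences and a low share of high scorers.

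**The case against.** The strongest reply is that nothing here contradicts the plan. It states no power, prevalence, SD or target difference for perceived stress, and a pre-set band for high stress is easy to interpret. A secondary outcome in an observational cohort need not be powered. This stands, and it limits the point to efficiency.

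Three stronger readings are tempting, and the article does not support them.

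- A reader might infer that most of the information is lost and the comparison is badly underpowered. Both depend on a score distribution and an effect size that the article does not give. Over the assumed range (p from 2% to 20%, d from 0.2 to 0.8) power on the dichotomy runs from about 8% to 99%. At d = 0.3 or below the full score is short of power too.
- A reader might infer that a null stress result would undermine the main hypothesis. The mechanism set out in the Background and Study Outcomes sections is autonomic and neurocardiogenic, and the Discussion assigns that question to the ECG markers. The questionnaire measures perceived stress, which is a different thing.
- A reader might infer that the score will be tested by chi-square and in no other way. Chi-square follows naturally from listing a frequency, but the statistical section does not name the scale and does not rule out analysing the score. An analysis plan that is not shown could add it.

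The last reply loses some force because the textbox does name extent as well as frequency for other outcomes. The dichotomy is therefore a stated choice of outcome, and not merely a detail left for later.

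**Conclusion.** The point holds as a minor efficiency improvement. The listed outcome is a dichotomy of a score that is collected in full. Under a normal shift with equal SD, any cut loses at least about a third of the information, whatever share scores high; the loss exceeds half only if that share is below about 21%. At 100 per group and d = 0.4, the assumed range of 2% to 20% gives about 20% to 55% power on the dichotomy, against about 81% on the full score.

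These sizes are illustrations. They rest on the assumed share of high scorers, the assumed difference and the shift model; a group difference confined to the upper tail would be less unfavourable to the cut. No claim in the plan is shown to be wrong.

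**What to change.** Name the total Perceived Stress Scale score as the analysed stress outcome. Compare it across the three groups by the rule already stated (one-way analysis of variance or Kruskal-Wallis), and for group 3 versus 1 and group 3 versus 2 by the stated Student t test. If the score proves clearly skewed, a rank test could replace the t test, but the plan names only the t test for two-group continuous data, so this should be recorded as a change to the statistical section. Keep the frequency of scores from 27 to 40 as a descriptive summary for each group.

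No extra data, visits or patients are needed. The cost is a small change to a secondary outcome of a registered study that is already recruiting (107 of 300 patients included at submission). It should be dated, justified and documented, preferably before the stress scores are compared between groups.
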